Multidisciplinary cardiac rehabilitation (CR) might be a successful alternative treatment in patients with SAP. CR improves achieving lifestyle targets and medication adherence [3, 8] and may also lead to symptom reduction through its systemic effects on cardiovascular function and by stimulating collateral artery development to bypass the partial coronary artery occlusion. Indeed, the EXCITE trial showed a significant improvement in coronary collateral flow index in response to 4 weeks of moderate- to high-intensity exercise [9]. In addition, Hambrecht et al. demonstrated that a 12-month training intervention resulted in a higher event-free survival rate and better exercise capacity compared to PCI [10]. To support the potential clinical benefits, a recent retrospective observational study in 18,383 patients with SAP showed that patients receiving exercise-based CR had 63% lower odds of all-cause mortality and 28% lower odds of acute myocardial infarction compared to PCI [11]. These observations highlight the potential of multidisciplinary CR as a primary treatment for SAP patients. Nevertheless, there have been no randomised controlled trials in the modern era that compared multidisciplinary CR to coronary revascularisation.

The first aim of this study is to compare the impact of a 12-month cardiac rehabilitation programme versus an invasive approach including coronary angiography and subsequent coronary revascularisation (i.e., usual care) in SAP patients with anginal complaints under OMT. We hypothesise that the 12-month CR programme will be at least equally effective as an invasive approach in reducing anginal complaints. The second aim is to evaluate the cost-effectiveness of the CR intervention compared to routine invasive care in SAP patients, as well as cardiovascular events, ischemic threshold during exercise, fitness, cardiovascular health, quality of life and psychosocial wellbeing.

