## Methods/design

### Design

This study is designed as a multicentre randomised controlled non-inferiority trial. Patients will be included at the cardiology department of eleven participating Dutch hospitals (Additional file 1). Patients are randomly allocated to a 12-month cardiac rehabilitation programme (intervention group) or usual care (control group). A total of 216 patients will be included, each group will consist of 108 patients (Fig. 1). All subjects are requested to provide written informed consent before study entry. Data are collected at baseline and after three, six, nine, and twelve months. The study has been approved by an ethical committee (METC Oost-Nederland, registration number 2021–12,942) and has been registered in the Netherlands Trials Register (NL9537). SPIRIT reporting guidelines were used for writing the study protocol [12].

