
### Sample size calculation

The sample size was calculated based on data from the ISCHEMIA trial, in which similar in- and exclusion criteria for SAP patients were applied as in our study [38]. The primary analysis will be based on the comparison between the two treatment arms at 12-month follow-up of the mean SAQ Summary score. The sample size assessment is based on comparing groups based on the 95% two-sided confidence interval for independent means, adjusted for baseline values (ANCOVA). The adjustment for baseline will provide an efficiency gain of 16% compared to an independent t-test, assuming a correlation of 0.4 (data from ISCHEMIA trial). The standard deviation for the SAQ summary score at 12-months is assumed to be 19 points (also data from ISCHEMIA trial). With a correction of 10% drop-out, 7% sample size gain will remain. Aiming for a power of 80% and under these assumptions, assuming equal means for both groups and a non-inferiority margin of 7 points, the required sample size is 195 patients. Accounting for 10% dropout, a total of 216 patients needs to be included.

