#### Cost analyses

For the cost analysis, the primary analysis will be based on the comparison between the two treatment arms. Cost is usually a parameter with a skewed distribution. If this occurs, as well as possible heteroscedasticity, cost analysis will be performed using a generalised linear model with a log ink function relating the conditional mean to independent variables and using a gamma distribution specifying the relationship between the variance and the mean.

For the utility analysis, health utility scores over time will be used. Quality adjusted life years will be calculated by taking the product sum of the health utility scores and the periods in-between successive measurements during the 12 months of follow-up according to the trapezium method. Utilities will be analysed using tobit regression.

The cost-utility analysis integrates costs and utilities to an Incremental Cost-Effectiveness Ratio with bootstrapped confidence intervals surrounding the point estimate of this ratio.

Analysis will be carried out in the statistical software package R.

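### The joint cost-utility result is a bootstrapped confidence interval on the ICER, which loses its decision meaning if the QALY difference is close to zero, as is likely in this trial

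*Protocol article*

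**What the plan says.** The Background of the protocol article states: "The second aim is to evaluate the cost-effectiveness of the CR intervention compared to routine invasive care". The same aim also covers events, ischaemic threshold, fitness and quality of life, and the Abstract lists cost-effectiveness among the secondary outcomes.

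Under Cost analyses, the effect measure is the QALY over 12 months: "Quality adjusted life years will be calculated by taking the product sum of the health utility scores", weighted by the time between measurements. Costs are compared between arms, with a gamma GLM if they are skewed, and utilities are analysed by tobit regression. Costs and utilities are then integrated into an "Incremental Cost-Effectiveness Ratio with bootstrapped confidence intervals surrounding the point estimate of this ratio". This is the only joint result that the article names.

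The Design section calls the study a "multicentre randomised controlled non-inferiority trial". The Sample size calculation section works from "assuming equal means for both groups and a non-inferiority margin of 7 points", on the SAQ Summary score. The Background and Discussion expect rehabilitation to relieve angina no less well than the invasive approach, and the Discussion expects that it may cost less.

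**The concern.** An ICER divides the cost difference by the QALY difference. If the QALY difference is small relative to its standard error, bootstrap denominators fall on both sides of zero. Two things then go wrong.

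- The ratio takes very large positive and negative values as the denominator approaches zero.
- Its sign is ambiguous. A negative ratio is either cheaper and better or dearer and worse. A positive ratio is either dearer and better or cheaper and worse.

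Sorted ratios then no longer run from favourable to unfavourable, so their 2.5th and 97.5th percentiles bound nothing that a decision-maker can use. At stake is the single statement that joins cost and effect, in a trial whose case for replacing revascularisation rests partly on lower cost.

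**Working it through.** **1. Evaluable patients per arm.** Inputs from the Sample size calculation section: SD 19, baseline correlation 0.4, margin 7, true difference 0, two-sided 95% interval, power 80%.

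- Adjusted SD = 19 × √(1 − 0.4²) = 17.41
- n per arm = 2 × [17.41 × (1.960 + 0.842) / 7]² = 97.1, or 194.3 in total; the plan states 195
- 195 / 0.9 = 216.7; the plan states 216

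The plan's figures are reproduced within rounding. About 97 evaluable patients per arm is used below.

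**2. Precision of the QALY difference.** The article gives no QALY SD, so 0.10 to 0.25 is assumed.

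- SE = SD × √(2/97) = 0.0144 at SD 0.10 and 0.0359 at SD 0.25

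**3. How often the interval includes zero.** For a true difference d, the probability that the 95% interval of the QALY difference includes zero is Φ(1.96 − d/SE) − Φ(−1.96 − d/SE).

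| True QALY difference | SD 0.10 | SD 0.15 | SD 0.20 | SD 0.25 |
|---|---|---|---|---|
| 0 | 95% | 95% | 95% | 95% |
| 0.02 | 71% | 85% | 89% | 91% |
| 0.05 | 6% | 36% | 59% | 71% |

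Example: d = 0.02 and SD 0.10 give d/SE = 1.39, and Φ(0.57) − Φ(−3.35) = 0.71. If the point estimate is 0, half of the bootstrap denominators are negative. If it is 0.02, 8% (SD 0.10) to 29% (SD 0.25) are.

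**4. What the percentile interval then looks like.** All cost inputs are assumptions: cost SD 6,000 per patient, cost difference −1,000 to −5,000, costs and QALYs uncorrelated. Normal draws stand in for the bootstrap replicates, with QALY differences of 0 to 0.02 and QALY SD 0.10 or 0.20. In every scenario the percentile limits of the ratio had opposite signs. They ran from roughly −0.5 to +0.4 million per QALY at the narrowest to roughly −5.5 to +5.5 million at the widest.

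**5. The same draws as net benefit.** Take a cost difference of −3,000, a QALY difference of 0, SD 0.10 and an illustrative threshold of 20,000 per QALY.

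- ICER percentile limits: about −3.2 to +3.1 million, although almost every draw shows a saving (about half cheaper and better, half cheaper and worse)
- Incremental net monetary benefit = 20,000 × QALY difference − cost difference = 3,000
- SE = √[(20,000 × 0.0144)² + (6,000 × √(2/97))²] = √(288² + 862²) ≈ 908
- 95% interval = 3,000 ± 1.96 × 908, about 1,200 to 4,800; the draws gave 1,206 to 4,789

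**6. Full bootstrap check.** There were 300 simulated trials with 97 per arm and 1,000 replicates each, gamma costs, control mean 9,000, cost SD 6,000 and true saving 3,000 (all assumed). The share of trials whose ICER percentile interval covers both signs was:

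| True QALY difference | SD 0.10 | SD 0.15 | SD 0.25 |
|---|---|---|---|
| 0 | 96% | 94% | 96% |
| +0.02 | 73% | 88% | 93% |
| +0.05 | 15% | 44% | 78% |

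At difference 0 and SD 0.15, the cost-difference interval lay wholly below zero in 94% of trials, yet 93% of those trials still had an ICER interval covering both signs. Net benefit at 20,000 excluded zero in 87% of trials.

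**The case against.** The strongest reply is that the article never assumes equal QALYs. A reader might infer from "assuming equal means for both groups" that the trial presumes no difference in effect and that the QALY difference must straddle zero. The text does not support this: the assumption concerns the SAQ score and serves the sample size only. QALYs are a 12-month area under a generic utility curve and could differ through an early procedure or through lifestyle effects, even with equal SAQ scores at 12 months. At a true difference of 0.05 and SD 0.10, straddling occurs in only 6% of trials. This stands, and it makes the point conditional.

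A reader might also infer that any bootstrapped ICER interval is invalid. The article does not name percentile limits, and intervals that order replicates by angle on the cost-effectiveness plane respect the quadrants. This stands too: the working shows failure of ordinary percentile limits only. Bootstrapping itself is sound.

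A third tempting reading is that the plan cannot address the economic aim at all. That goes too far. Costs and utilities are also compared separately, and a budget impact analysis is planned, so a clear saving would be seen.

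Finally, the article's silence on the plane, the acceptability curve and a threshold is not a fault, since a fuller economic plan may hold them. What remains is a choice that the article does make: its one joint result is an interval on the ratio.

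**Conclusion.** The concern holds in conditional form. If the true QALY difference lies between 0 and 0.02, zero falls inside its 95% interval in about 71% to 95% of trials over assumed QALY SDs of 0.10 to 0.25, and ordinary percentile limits of the ICER would usually be unusable. At 0.05 the range is 6% to 71%. A small difference is likely given the non-inferiority premise, but the article does not state one. The QALY SDs, costs and threshold are all assumptions; only the evaluable sample comes from the plan. The damage is confined to the joint cost-utility summary. The primary non-inferiority test, the sample size and the separate cost and utility comparisons are unaffected. The change should be made, but it is not critical to the trial.

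**What to change.** Keep the joint bootstrap of costs and QALYs and change what is reported from it:

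- Make incremental net monetary benefit, with a bootstrap 95% interval over a pre-stated willingness-to-pay range, the inferential result.
- Show the replicates on the cost-effectiveness plane and give the acceptability curve.
- Report the ICER as a point estimate with its quadrant, without an interval on the ratio.

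This needs no new data, visits or patients, only wording in the analysis plan, settled before comparative results are seen so that neither summary nor threshold is chosen afterwards. The small cost is that a willingness-to-pay range must be fixed in advance and the conclusion may depend on it. In the full bootstrap check (QALY SD 0.15, difference 0), net benefit excluded zero in 87% of trials at 20,000 per QALY but in only 34% at 80,000. The interval stays finite and ordered in both cases and shows that dependence openly.

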## Discussion

The PRO-FIT study is the first study directly comparing the impact of a conventional invasive approach versus a multidisciplinary cardiac rehabilitation programme as a primary treatment in SAP patients on anginal complaints. The CR intervention is multidisciplinary and includes exercise training to improve coronary perfusion and behavioural change strategies in combination with modern technology to optimise long-term adherence to a healthier lifestyle and thereby reduce cardiovascular morbidity. The objective of this study is to investigate whether a comprehensive CR-intervention is at least equally effective in reducing anginal symptoms as a conventional, invasive approach.

In 2004 Hambrecht et al*.* highlighted the potential benefits of exercise training in SAP [10]. In this randomised controlled trial, 100 patients with an angiographically objectified stenosis were randomly assigned to PCI or a 12-month exercise intervention. The training intervention resulted in a higher event-free survival rate and better exercise capacity after 12 months compared to PCI. The results were achieved using exercise training only, and therefore may even underestimate the true potential of lifestyle changes for this patient group. Past years, studies have demonstrated the benefit of a multimodality programme over exercise training only as multimodality programs impact several levels of a healthy lifestyle [39, 40]. By offering SAP patients a multidisciplinary CR programme, addressing other risk behaviour as well, the clinical benefits may be superior to exercise training only. On the other hand, the development of drug eluting stents and the advancement of antiplatelet therapy improved the clinical outcomes of invasively treated patients in the period following Hambrecht’s trial [41–43]. Given these advancements, results of our study and Hambrecht’s trial might not be corresponding.

Besides the potential benefits of CR as a first line treatment for SAP on clinical outcomes, CR may also be more cost-effective than invasive treatment. A first indication for this hypothesis is provided by Hambrecht’s CR intervention, which demonstrated CR to be more cost-effective than PCI [10]. As health care costs are mounting, primarily by a growing population and an unhealthy lifestyle, low-cost alternatives to invasive procedures are important to reduce the burden of stable cardiovascular disease, both for patients as for society. If CR demonstrates to be effective, it is important to realise that CR is also scalable and affordable. For this purpose, we aim to conduct the CR intervention through first line physiotherapists using an already existing network with nationwide coverage. If proven successful, this approach allows for successful nationwide implementation and will lower the pressure on hospital resources and staff. Furthermore, our CR programme has an early transition from centre-based CR to telerehabilitation to improve cost-effectiveness, as previous studies showed lower social costs in telerehabilitation, particularly due to lower absenteeism [44, 45].

The Ischemia trial already showed that revascularisation does not reduce the risk of ischemic cardiovascular events or death from any cause compared to OMT alone, but does reduce anginal complaints. Our study is designed to investigate whether OMT supplemented with a comprehensive CR-intervention reduces anginal complaints just as effectively as revascularisation. There is a strong, (patho)physiological rationale underlying this concept. By choosing PCI as the primary target, treatment is limited to addressing a local obstruction only. However, SAP patients often demonstrate poor vascular health at systemic level, and are at increased risk of developing cardiovascular events later in life [9]. The local focus of PCI does not improve the overall endothelial function nor prevent future obstructive plaques causing subsequent procedures. Therefore, a lifestyle intervention, aiming to improve both local perfusion and function of the entire vascular system, might be a better alternative to a local, invasive strategy in these patients.

Replacing invasive interventions with lifestyle interventions is not common in contemporary medicine, although some examples exist. Patients with peripheral artery disease for example, are currently referred for first line supervised exercise training as a (cost-)effective treatment, whereas invasive vascular interventions to target the local stenosis used to be standard treatment upon presentation of complaints. Exercise training demonstrated superior effects on intervention-free survival, walking distance and quality of life compared to invasive vascular interventions [46, 47]. Following this evidence, international guidelines recommend exercise training as a treatment of first choice in patients with intermittent claudication [48]**.** In analogy to stable angina, these studies highlight that addressing the systemic vascular problem, rather than focusing on the local lesion, may improve clinical outcomes. In relation to stable angina, the recent retrospective observational study by Buckley et al*.* supports this concept and emphasises the potential of CR as a treatment for SAP patients, showing a significant reduction in all-cause mortality and myocardial infarction compared to PCI [13]. This clinical example around peripheral artery disease also highlights the importance of studies that directly compare invasive *versus* non-invasive strategies on clinically relevant outcomes.

In conclusion, we hypothesise that multidisciplinary CR is at least equally effective in reducing anginal complaints as an invasive approach in patients with stable angina pectoris. This comparison is highly relevant, since CR may be related to lower costs (and complication rates) compared to PCI, whilst CR is aimed at improving systemic health status and lowers risks for other cardiovascular diseases. If proven successful, this study will have a significant impact on the daily care of these patients as coronary revascularisations can largely be replaced by multidisciplinary CR; a less invasive, less costly and better sustainable treatment.

### Trial status

The inclusion of patients has started in February 2022. As of April 2023, we have enrolled 38 patients in the study. Recruitment will continue until the complete sample size is achieved.

## Data Availability

Not applicable.

## Abbreviations

ANCOVA: Analysis of covariance
CAG: Coronary angiogram
CMR: Cardiac magnetic resonance imaging
CR: Cardiac rehabilitation
EQ-5D-5L: EuroQol 5-level EQ-5D
FFR: Fractional flow reserve
HADS: Hospital Anxiety and Depression Scale
HbA1c: Haemoglobin A1c
HRR: Heart rate reserve
IMCQ: Imta Medical Cost Questionnaire
IPCQ: Imta Productivity Cost Questionnaire
OMT: Optimal medical therapy
PCI: Percutaneous coronary intervention
PEP: Psycho-educational prevention module
PET: Positron emission tomography
SAP: Stable angina pectoris
SAQ: Seattle angina questionnaire
SBQ: Sedentary behaviour questionnaire
SMS: Short message service
SPECT: Single photon emission computed tomography
SQUASH: Short questionnaire to assess health-enhancing physical activity
Wpeak: Peak power output
1RM: One-repetition maximum
